### Conventional exercise rehabilitation group (EG)

3.7

Participants in the conventional exercise rehabilitation group will undergo a combined aerobic and resistance training intervention, following a structured moderate period high-intensity resistance training (MP-HI-RT) + moderate period low-intensity aerobic exercise (MP-LI-AE) (23). Participants will engage in three 40-min sessions per week, guided by professional two-way live video tutorials. Each session consisted of 5 min of warm-up, 30 min of core resistance training with resistance bands, and 5 min of cool-down exercises. The resistance load will be determined based on baseline muscle strength assessments to ensure appropriate intensity for each participant. Additionally, participants will be encouraged to engage in self-paced walking exercises outside of the supervised sessions, with walking intensity adjusted according to their pre-measured aerobic capacity. Participants who withdrew from the study will be asked to provide their reasons for discontinuation.

### Control group (CG)

3.8

Participants in the control group will not receive specific exercise guidance and will be instructed to maintain their usual daily activities. Researchers will conduct regular monthly follow-ups to assess participants’ status and to confirm that they do not engage in additional exercise interventions during the study period.

### Technology support and internet literacy

3.9

To ensure all participants can smoothly access the remote live sessions, brief internet literacy training will be provided before the start of the program. During this training, each participant’s ability to log in to the secure two-way video conferencing platform will be verified. If a participant is unable to operate the platform independently, their family members or caregivers will receive clear instructions and training to assist them. All sessions will be delivered via a two-way live format, and live session streams will be backed up to the cloud within the platform for internal monitoring purposes only.

In addition to the instructors, a designated research team member will be online throughout each live session to monitor technical stability and provide immediate assistance if needed. Participants will also have access to real-time technical support during class hours via instant messaging or phone contact, ensuring any network or access issues can be resolved promptly.

### Adherence monitoring

3.10

To ensure participant compliance and maximize the effectiveness of the interventions, all participants in the Qigong group and the conventional exercise rehabilitation group will be required to submit weekly practice logs reporting their training completion, experience, and any discomfort. Participants may submit these practice logs in written form via email, text message, or instant messaging apps, depending on their preference and convenience. Alternatively, participants who find it difficult to submit written logs will have the option to report verbally through a scheduled phone call with a designated member of the research team. For each participant, a designated research member will maintain regular contact. If a participant does not submit their weekly report on time, the research team will proactively follow up by phone or instant messaging apps to remind them to submit their practice log. To further promote accountability and adherence, each participant will receive a minimum of two phone check-ins per month.

During these calls, the research team will:

Review the participant’s training progress and address any questions about the intervention.Provide coaching tips or practical advice to help overcome any difficulties in following the exercise program.Discuss potential barriers to adherence (e.g., time constraints, technical issues) and offer feasible solutions.Encourage participants to continue practicing regularly and highlight the importance of consistent participation for achieving the expected benefits.

These follow-up communications will be documented in the study records. If a participant repeatedly fails to submit practice logs or shows signs of poor adherence, the research team will provide additional personalized guidance and, if necessary, involve family members to support the participant’s continued engagement.

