#### Exclusion criteria

3.2.2

Prior experience with systematic Baduanjin Qigong training or resistance exercise programs.Severe cardiovascular disease, musculoskeletal disorders, or other conditions that significantly impair physical activity.Severe mental illness or cognitive dysfunction (MMSE score <24).Recent deep brain stimulation (DBS) treatment.Inability to access the internet for remote training.

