### Subject grouping

3.3

All participants will receive a comprehensive explanation of the study’s objectives, procedures, potential benefits, and possible risks before the trial. They will voluntarily sign an informed consent form and will be informed that they can withdraw from the study at any stage without any adverse consequences. After completing the informed consent process, participants will be randomly assigned in a 1:1:1 ratio to one of three groups—the Qigong group (QG), the conventional exercise rehabilitation group (EG), or the control group (CG)—using a computer-generated random number table. Participants in both the Baduanjin Qigong and conventional exercise rehabilitation groups will receive three remote live training sessions per week and will be encouraged to perform an additional two to three self-guided sessions weekly. Participants in the control group will maintain their usual daily activities without additional exercise intervention, but will be required to complete regular follow-ups and assessments.

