### Statistical analysis

3.17

A mixed-effect model will be employed to analyze the experimental data, accounting for individual variability. The model will assess the random effect of participants while adjusting for baseline variables. Baseline characteristics will be compared between groups using appropriate statistical tests (e.g., one-way ANOVA for continuous variables, chi-square test for categorical variables) to ensure group equivalence prior to intervention. If any significant baseline differences are found, they will be adjusted for in the subsequent analyses. To account for differences in exercise intensity and total dose between groups, weekly exercise volume (MET-hours/week) will be calculated and included as a covariate in the mixed-effect model. Intergroup comparisons will be conducted without multiple comparison adjustments. The differences in intervention effects among the three groups will be calculated and expressed as effect sizes with 95% confidence intervals (CIs). For outcome analyses, mixed-effect models will be primarily employed to analyze repeated measures across time points. When analyzing between-group differences at individual time points, one-way ANOVA or Kruskal-Wallis test will be applied, depending on data distribution and normality assumptions. Pairwise post-hoc comparisons will apply Bonferroni correction. All statistical analyses will be conducted using SPSS 26.0 and R 4.0.2, with a significance level of *p* < 0.05.

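### Exercise exposure is recorded on different scales by arm, so the planned weekly MET-hours covariate has no stated weekly source in controls and none for non-assigned exercise in the active arms

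*Protocol article*

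**What the plan says.** All references are to the protocol article.

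- **Active arms, Section 3.10.** Logs are weekly and confined to QG and EG: "all participants in the Qigong group and the conventional exercise rehabilitation group will be required to submit weekly practice logs reporting their training completion", together with experience and discomfort. The section also says that "each participant will receive a minimum of two phone check-ins per month". The listed content of those calls is progress with the intervention, coaching, barriers to adherence and encouragement.
- **Active arms, Sections 3.3 and 3.7.** Beyond three live sessions a week, participants in both arms "will be encouraged to perform an additional two to three self-guided sessions weekly". EG participants are also encouraged to walk at their own pace.
- **Control arm (CG), Section 3.8.** Participants "will be instructed to maintain their usual daily activities". Researchers make contact monthly, among other things "to confirm that they do not engage in additional exercise interventions during the study period".
- **Analysis, Section 3.17.** To allow for differences in intensity and total dose between groups, "weekly exercise volume (MET-hours/week) will be calculated" and entered in the mixed model. No data source is named.
- **Partial safeguards.** Section 3.2.2 excludes "Prior experience with systematic Baduanjin Qigong training or resistance exercise programs". Section 3.18 says participants will not be told the details of the other arms' interventions.

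**The concern.** A weekly volume meant to account for dose differences between groups needs comparable weekly data from all three. The monitoring as described gives weekly data on the assigned programme in two arms and a monthly confirmation in the third. Two kinds of exposure then fall outside the stated record:

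- the weekly amount of exercise in controls;
- any exercise other than the assigned programme in QG and EG, including the other arm's modality.

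What is at stake is interpretation. Uptake of exercise by controls shrinks QG-CG and EG-CG. Uptake of the other modality shrinks QG-EG, the comparison behind the third objective in Section 2. If either contrast came out null, the trial would have little or nothing with which to separate a true absence of difference from dilution. This remains so even if exercise volume is dropped from the model.

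The entry criteria do not settle it. They exclude earlier Baduanjin and resistance programmes but not current aerobic exercise, tai chi or regular walking, and the article lists no exercise level before randomisation.

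**Working it through.** **Step 1: set the sections side by side.**

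| Exposure | QG and EG | CG |
|---|---|---|
| Assigned programme | Weekly log, about 12 in 12 weeks | Not applicable |
| Other exercise | No stated record | Monthly check for added programmes, about 3 in 12 weeks |
| Weekly amount of all exercise | No stated source | No stated source |
| MET-hours/week (Section 3.17) | Planned | Planned, since it is to adjust for differences between groups |

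The last two rows do not fit together. Section 3.10 sets out the content, routes, reminders and calls for the logs in some detail, so confining them to two arms reads as a stated choice and not merely as brevity.

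**Step 2: inputs for an illustration.** The plan gives no contamination rate, so there is no figure of its own to reproduce on this point. From Section 3.19: difference 5 points on PDQ-39, SD 10.5, 42 evaluable per arm, two-sided 0.05. The uptake proportions c are assumptions. (The dropout step reproduces: 42/0.85 = 49.4, rounded up to 50. The 42 itself does not reproduce for a two-sided pairwise comparison at 80% power, which needs 70 per arm at 5/10.5. That is a separate matter, and 42 is used here only as the plan's evaluable number.)

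**Step 3: control uptake.** If a share c of controls gains the full benefit, the difference becomes 5(1 − c). Power is Φ(Δ/(10.5·√(2/42)) − 1.96), with 10.5·√(2/42) = 2.291. For c = 0: 5/2.291 = 2.182, less 1.96 = 0.222, giving 0.59.

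| Assumed c | Difference | Power, 42 per arm | n per arm for 80% |
|---|---|---|---|
| 0 | 5.0 | 0.59 | 70 |
| 0.10 | 4.5 | 0.50 | 86 |
| 0.20 | 4.0 | 0.42 | 109 |
| 0.30 | 3.5 | 0.33 | 142 |

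**Step 4: uptake between the active arms.** Let a and b be the QG and EG effects and c the share in each arm taking up the other modality.

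- *Adding it, effects additive:* QG averages a + cb and EG averages b + ca. The difference is (1 − c)(a − b).
- *Adding it, only the larger effect counts (say a > b):* QG averages a and EG averages (1 − c)b + ca. The difference is again (1 − c)(a − b).
- *Swapping entirely:* QG averages (1 − c)a + cb and EG averages (1 − c)b + ca. The difference is (1 − 2c)(a − b).

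At c = 0.10 and 0.20, adding leaves 90% and 80% of the difference, a loss of 10-20%. Swapping leaves 80% and 60%, a loss of 20-40%.

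**The case against.** The strongest objection is that a journal article condenses the full protocol. Log fields, participant instructions and baseline forms are commonly left to that document, and the commitment to compute weekly MET-hours itself suggests that some volume data will be collected. This stands as a limit: the article does not show that no such data will exist. It does not remove the mismatch, because Sections 3.8 and 3.10 describe who reports what and how often, and that description does not supply the variable in Section 3.17.

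Several stronger readings are tempting and not supported:

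- *Control contamination goes unmeasured.* It does not. Section 3.8 schedules a check for exactly this. It is coarse and on a different scale from the other arms. Whether it prompts the expected answer cannot be judged, since the questions are not shown.
- *Nothing guards against crossover.* Section 3.18 withholds details of the other arms, and someone who dropped the assigned programme for the other one should appear in the logs as not completing. Both help. Neither prevents or records adding the other modality.
- *Crossover would cost 20-40% of QG-EG.* At 10-20% uptake that requires participants to swap modality entirely. Adding it costs 10-20%.
- *Exercise that controls already do biases the trial.* It belongs to a usual-activity comparator, and randomisation balances it in expectation.

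It is also fair to say that a log does not restore a diluted difference, and that logging controls may make them more active. Both are true and bear on how the remedy is described. The case for the remedy is that a null result becomes interpretable.

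**Conclusion.** The concern holds in a limited form. Exposure is recorded weekly for assigned training in QG and EG and monthly, as a confirmation, in CG, while the analysis section plans a weekly between-group volume. As described, that variable lacks a weekly source in controls and lacks non-assigned exercise in the active arms. Sections 3.8, 3.10 and 3.17 must be reconciled.

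The size is illustrative only. With an assumed 10-30% of controls gaining the full benefit, a 5-point difference becomes 4.5-3.5 points, and pairwise power at 42 per arm goes from 0.59 to 0.50-0.33. With an assumed 10-20% in each active arm adding the other modality, QG-EG loses 10-20%. The true rates are unknown and, as the article stands, would remain largely unknown after the trial. The change is worth making before recruitment goes far, because exposure not recorded at the time cannot be reliably recovered later.

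**What to change.** 1. Use one short record of all exercise, assigned or not (type, minutes, perceived effort), on the same weekly schedule in all three arms, through the email, messaging and phone routes of Section 3.10 and with the same reminders.
2. Collect one such record before randomisation and use that exercise level as a baseline covariate.
3. Extend the statement in Section 3.8 so that starting an additional exercise programme is recorded in QG and EG as well as CG, and report non-assigned exercise by arm alongside the contrasts.
4. In Section 3.17, name this record as the source of MET-hours/week. Because volume after randomisation is itself a consequence of the assigned arm, use it descriptively or in supportive analyses.
5. If the full protocol already has such a form, say so and align the three sections with it.

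The cost is protocol wording and a one-page record for 50 more participants over contact routes that already exist. The downside is that logging may make some controls slightly more active.

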## Objectives

2

To assess the feasibility and effectiveness of Internet-based remote intervention as a practical approach for exercise rehabilitation in individuals with PD.To determine whether remote Baduanjin Qigong intervention enhances quality of life and physical function in patients with mild to moderate PD.To compare the therapeutic effects of remote Baduanjin Qigong intervention with those of conventional exercise rehabilitation (aerobic and resistance training) in alleviating clinical symptoms and improving functional outcomes in PD patients.

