#### MDS-UPDRS part I

3.14.3

MDS-UPDRS represents one of the most widely used tools to assess PD progression (27). MDS-UPDRS Part I will be used in this study to assess non-motor experiences of daily living in individuals with PD. Part I consists of patient-reported items evaluating symptoms such as cognitive impairment, mood disturbances (e.g., depression, anxiety), sleep problems, pain, urinary issues, and fatigue. Higher scores indicate greater severity of non-motor symptoms. MDS-UPDRS Part I has demonstrated high internal consistency (Cronbach’s *α* = 0.85), small floor and ceiling effects (2 and 0%, respectively), and good concurrent validity (correlation with the original UPDRS Part I: r = 0.81, *p* < 0.001) (28). Its inclusion in this study will provide a comprehensive evaluation of the non-motor aspects of patient well-being, complementing the broader quality of life assessments captured by the PDQ-39 and SF-36.

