### Blind method

3.18

Subjects will be randomly assigned to one of three groups (QG, EG, or CG). The details of randomization and allocation concealment are described in Section 3.4.1.

Blinding procedures will be implemented to minimise bias:

Participants will be aware of their assigned intervention, but will not be informed about the details of other group interventions since all remote sessions will be delivered via the remote platform.Outcome assessors will be blinded to group allocation to prevent measurement bias during data collection, and statisticians will be blinded during statistical processing until the final analysis stage.Intervention facilitators will only know their specific group assignment and will not be part of data collection or analysis.

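### Calls that stress expected benefit go only to the exercise arms, and the primary outcomes are self-reports by unblinded participants, so a Qigong–control quality-of-life difference can speak only for the whole remote programme

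*Protocol article*

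**What the plan says.** All references are to the protocol article.

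- **Objective (section 2).** The second objective is "To determine whether remote Baduanjin Qigong intervention enhances quality of life and physical function in patients with mild to moderate PD". It names no comparator, and CG is the only arm without an exercise programme.
- **Exercise arms (section 3.10).** The section opens by stating that "all participants in the Qigong group and the conventional exercise rehabilitation group will be required to submit weekly practice logs". It adds that "each participant will receive a minimum of two phone check-ins per month". Of the four listed call items, three cover training progress and questions, coaching tips, and barriers to adherence. The fourth is to encourage regular practice and "highlight the importance of consistent participation for achieving the expected benefits".
- **Control arm (section 3.8).** "Researchers will conduct regular monthly follow-ups to assess participants’ status and to confirm that they do not engage in additional exercise interventions". No mode of contact is given.
- **Outcomes (sections 3.13 and 3.14).** The primary outcomes are PDQ-39, SF-36 and MDS-UPDRS Part I. PDQ-39 is called a questionnaire, SF-36 is a health survey, and of the third the protocol says "Part I consists of patient-reported items evaluating symptoms".
- **Blinding (section 3.18).** Participants know their own arm but are not told the details of the others. "Outcome assessors will be blinded to group allocation to prevent measurement bias during data collection". Statisticians are blinded until the final analysis stage.

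**The concern.** Blinding an assessor works where the assessor makes the measurement, as in the timed and measured tests of section 3.15. For the three primary instruments the participant supplies the answer, and the participant is not blinded. The measurement safeguard in section 3.18 therefore does not reach the place where an expectation effect would enter.

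An exercise trial cannot avoid open allocation. A standing instruction to remind respondents of expected benefit is avoidable. It is repeated through the 12 weeks, falls on one side of the QG–CG contrast and works in the direction of the hypothesis. If QG scores better than CG on quality of life, the plan as written attributes this to Baduanjin, although the difference would also contain prompting, coaching and attention.

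**Working it through.** **1. Planned contact over 12 weeks** (12 / 4.345 = 2.8 months)

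| | QG and EG | CG |
|---|---|---|
| Phone check-ins or follow-ups | at least 2 × 2.8 = 5.5, so 5 to 6 | 1 × 2.8, about 3 |
| Reminder of expected benefit | listed as call content | not listed |
| Weekly practice logs | 12 | none |
| Live 40-minute sessions | 3 × 11 = 33 to 3 × 12 = 36 | none |
| Live hours | 33 × 40/60 = 22 to 36 × 40/60 = 24 | 0 |

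The lower session count leaves out week 1, which section 3.6 gives to small-group instruction in QG. Two things follow. The live sessions, not the calls, are the main source of unequal attention between QG and CG. QG and EG share the same scheme, so the third objective, which compares them, is balanced on planned contact and on the benefit reminder.

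**2. Does anything in the plan offset the QG–CG imbalance?**

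- Section 3.17 adjusts for weekly MET-hours. That measures exercise volume, not contact or expectation.
- Section 3.18 withholds details of the other arms. This helps in part, but controls still know that they have no exercise programme.
- The limitations in section 4 do not mention the imbalance.

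**3. How much could it matter?** The documents give no size for a non-specific shift, so the following is an illustration over an assumed range. Inputs from section 3.19 are a target difference of 5 PDQ-39 points, SD 10.5, two-sided alpha 0.05, 42 per group before dropout and 50 after.

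The dropout step in the plan reproduces: 42 / 0.85 = 49.4, so 50. The 42 does not: 2 × (1.960 + 0.842)² × 10.5² / 5² = 69.2, so 70 per group. That is a separate matter on which this point does not depend. Both 42 and 50 are used below.

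Let the specific Qigong effect be zero and the non-specific shift be b points. Then SE = 10.5 × √(2/n), which is 2.29 at n = 42 and 2.10 at n = 50. The chance of a significant QG–CG difference is Φ(b/SE − 1.96) + Φ(−b/SE − 1.96).

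| b (assumed, points) | b as share of the 5-point target | n = 42 | n = 50 |
|---|---|---|---|
| 0 | 0% | 5.0% | 5.0% |
| 1 | 20% | 7.2% | 7.6% |
| 2 | 40% | 14.1% | 15.9% |
| 3 | 60% | 25.8% | 29.8% |
| 4 | 80% | 41.5% | 47.8% |
| 5 | 100% | 58.8% | 66.3% |

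For b = 2 and n = 42: 2/2.29 = 0.873; Φ(−1.087) + Φ(−2.833) = 0.138 + 0.002, which is 0.141 before rounding the parts. This b covers every non-specific influence, including the live sessions. The share due to the benefit reminder alone cannot be separated.

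**The case against.** The strongest reply has five parts.

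- **A contact-matched arm exists.** EG has the same number of live sessions and the same logs and calls. This stands. It confines the point to QG–CG, and it supplies the contrast to read beside it.
- **The second objective already concerns a remote intervention, so contact is part of what is tested.** A whole-programme reading is legitimate. The protocol does not state it, however, and its wording credits the benefit to Baduanjin.
- **The benefit line is one item of four and names no outcome or size of improvement.** This is true. A reader might infer that staff tell participants what improvement to report, but the text does not go that far.
- **Expectation arises anyway.** Under section 3.3, all participants hear about possible benefits before the trial. Dropping the line therefore reduces the expectation effect and does not abolish it. That explanation is given to every arm, whereas the calls repeat the message in two arms only.
- **The blinding section does give some protection.** A reader might infer that it does nothing for the primary outcomes. That is too strong: statistician blinding applies to them, and withholding details of the other arms helps in part. Only assessor blinding is ineffective for self-reports.

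The phrase about each participant's check-ins could be read to include CG. The section opens with QG and EG, however, and the call content concerns training, so the narrower reading is the natural one.

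**Conclusion.** The point holds for the QG–CG contrast in self-reported quality of life. The plan adds a one-sided, avoidable source of expectation, and assessor blinding cannot remove it. It does not hold for QG–EG, and it applies much less to the physical-function tests, which blinded assessors measure.

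The size is unknown. It would be tempting to say that expectation accounts for 20–40% of the 5-point target, but that only restates an assumed 1 to 2 points; the documents support no figure. Nor do they support the conclusion that the second objective cannot be answered. It can be answered for the programme as delivered, though not for Baduanjin apart from contact and support.

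The conclusion rests on reading the section 3.10 calls as confined to QG and EG, and on the protocol's own description of the primary instruments. This is a worthwhile, inexpensive improvement rather than a fatal flaw.

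**What to change.** 1. **Section 3.10:** remove the reference to expected benefits from the call content. Keep the neutral items: progress, questions, barriers, technical help and encouragement to practise. If recruitment has begun, apply this to the remaining calls and record the date of the change.
2. **Section 3.18:** state that assessor blinding protects the performance tests, and that PDQ-39, SF-36 and MDS-UPDRS Part I are open-label self-reports.
3. **Interpretation:** state that a QG–CG quality-of-life difference is the effect of the whole remote programme, exercise plus contact and support. Read it alongside the contact-matched QG–EG contrast and the assessor-blinded performance tests. Add the imbalance to the limitations in section 4.

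The cost is some redrafting and slightly weaker motivational prompting. Matching the frequency of control contact is optional: about 3 extra contacts × 50 controls = 150. It would not equalise attention, because 22 to 24 hours of live sessions would remain on one side only.
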